## Abstract

**Background:**

Publicly reported performance on quality measures is intended to enable patients to make more informed choices. Despite the growing availability of these reports, patients’ use remains limited and disparities exist. Low health literacy and numeracy are two barriers that may contribute to these disparities. Patient navigators have helped patients overcome barriers such as these in other areas, such as cancer care and may prove useful for overcoming barriers to using publicly reported quality data.

**Methods/Design:**

The goals of this study are: to determine the efficacy of a patient navigator intervention to assist low-income pregnant women in the use of publicly available information about quality of care when choosing a pediatrician; to evaluate the relative importance of factors influencing women’s choice of pediatric practices; to evaluate the effect of the intervention on patient engagement in management of their own and their child’s health care; and to assess variation in efficacy of the intervention for sub-groups based on parity, age, and race/ethnicity. English speaking women ages 16 to 50 attending a prenatal clinic at a large urban medical center will be randomized to receive an in-person navigator intervention or an informational pamphlet control between 20 to 34 weeks of gestation. The intervention will include in-person guided use of the Massachusetts Health Quality Partners website, which reports pediatric practices’ performance on quality measures and patient experience. The primary study outcomes will be the mean scores on a) clinical quality and b) patient experience measures.

**Discussion:**

Successful completion of the study aims will yield important new knowledge about the value of guided website navigation as a strategy to increase the impact of publicly reported quality data and to reduce disparities in use of these data.

**Trial registration:**

ClinicalTrials.gov #NCT01784575

## Background

Every year, more than 4 million children are born in the US [1]. Shortly after delivery, parents face the important task of selecting a pediatrician for their new baby. Receiving recommended care from a pediatric provider can impact child health, and is particularly important in the first two years of life [2-8]. Variation in care quality exists between health plans, communities, hospitals, outpatient practices, and providers [9-11], but patients may not be aware that this variation exists [12].

One way to help patients become aware of differences in physician performance is through the public reporting of quality measures. If patients use information about performance to choose practices with higher quality care or if public reporting stimulates providers to engage in quality improvement activities, public reporting of quality information should result in better patient outcomes [13]. However, the impact on patients’ choices has been limited to date [14], perhaps in part because of a lack of awareness of publicly reported quality data [15]. Even when patients are aware of websites reporting health care quality data, the information may not effectively reach patients because the websites are difficult to navigate and the data are difficult to interpret [16-19]. This failure to reach patients may be especially pronounced in vulnerable populations, such as those with lower health literacy [18,20].

Massachusetts Health Quality Partners (MHQP) is a non-profit organization that has been working to improve care quality in Massachusetts since 1995. The organization works with stakeholders, including patients, physicians, insurance companies, and academic partners to collect and report quality-of-care data in the Commonwealth. Since 2005, MHQP has included a quality reporting tool known as “Quality Insights” on its website [21]. These reports show adult and pediatric practices’ performance on clinical quality and patient experience measures (Table 1). These reports have been recognized for excellence in methodology and accessibility, and are, to our knowledge, the only source of publicly reported, ambulatory pediatric practice quality data in Massachusetts. The website is currently only available in English.

**Table 1 T1:** Categories of pediatric clinical quality and patient experience reported on the MHQP website

**Clinical quality**	*Asthma care*	*Well child visits*	*Pediatric medications and testing*	*Women’s health*	
	Medication for children ages 5- to 11 years	Well visits for children 0 to 15 months of age	Correct testing for strep	Chlamydia screening (ages 16 to 20 years)	
		Well visits for children ages 3 to 6 years	Correct antibiotic use for upper respiratory infections		
		Well visits for adolescents ages 12 to 21 years	Follow-up for children starting medication for ADHD		
**Patient experience**	How well doctors communicate with patients	How well doctors coordinate care	How well doctors know their patients	How well doctors give preventive care advice	Willingness to recommend

*ADHD* Attention deficit hyperactivity disorder.

Patient navigators assist patients in overcoming barriers to achieving care goals. Traditional patient navigators have successfully helped patients navigate complex care environments and achieve better health outcomes [22-24], with those at risk for low health literacy and numeracy benefiting the most [25-27]. These traditional navigator functions may assist patients attempting to access and interpret publicly reported information about quality of care, tailoring the assistance to the patient’s needs. Pregnant women are generally healthy and have ample time to explore options for pediatric care along with multiple contacts with the healthcare system, making this condition ideal for a navigator intervention to support use of publicly reported quality data.

We plan to implement a randomized controlled trial (RCT) design to test the efficacy of a patient navigator intervention. The goal of the intervention is to educate women about the availability and meaning of quality measures in pediatrics and to review information about the quality of local pediatric practices, enabling them to make a more informed decision about where to obtain care for their child.

## Methods/Design

### Study objectives

The primary study outcomes are a) the mean clinical quality score and b) the mean patient experience score of the pediatric practices selected. The study goals are: to determine the efficacy of a patient navigator intervention to assist low-income pregnant women in the use of publicly available information about quality of care when choosing a pediatrician; to evaluate the relative importance of factors influencing women’s choice of pediatric practices; to evaluate the effect of the intervention on patient engagement in management of their own and their child’s health care; and to assess variation in efficacy of the intervention for sub-groups based on parity, age, and race/ethnicity. This study is approved by the Baystate Medical Center Institutional Review Board.

### Study design

This study is a two-arm RCT of patient navigators. Participants are randomized to either the intervention arm (navigator plus informational pamphlet) or the control arm (informational pamphlet only).

### Study site and participants

The Obstetric and Gynecology Clinics at Baystate Medical Center, located in Springfield, Massachusetts, perform approximately 1,500 to 1,800 deliveries annually. The clinics are staffed by eleven obstetricians, six nurse practitioners, and twenty-one house staff from the Baystate Medical Center (BMC)/Tufts University School of Medicine (TUSM) residency training program in obstetrics and gynecology. The majority (89%) of the women attending the clinic are insured through Medicaid, the national public insurance available to women with no employer-based insurance and/or a low-income level [28]. Children of women who qualify for Medicaid often also qualify for this public insurance. A survey undertaken by the American Academy of Pediatric in the year 2000 showed nearly 95% of pediatric practices in Massachusetts accepted all patients with public health insurance [29], but practices may elect to limit the number of patients they take with any type of insurance. Of these, 57% are Hispanic (predominantly from Puerto Rico), 17% are African-American, 23% are non-Hispanic white, and 3% are of other race/ethnicity [28]. Among Hispanic women attending the clinic, nearly 80% prefer speaking English [28]. English-speaking women ages 16 to 50 years between 20 and 34 weeks of pregnancy will be eligible for enrollment in the study.

### Recruitment and informed consent

Women will be given a one-page study fact sheet by office staff when they first present to the Wesson Women’s Clinic. When women check in for their prenatal visit during weeks 20 to 34 of gestation, they will be reminded of the study by one of the two trained patient navigators and will be given the one-page fact sheet again as a reminder of study goals. If a woman expresses interest in enrolling, informed consent will then be obtained. Baseline data will be collected and the patient will be randomly assigned to the navigator intervention or the pamphlet control. Randomization will be stratified based on parity because women who have already selected a pediatric practice for their older children may be less likely to change practices based on quality performance alone. If randomized to the intervention arm, the first intervention session will ensue. If in the control arm, the patient will be given an informational pamphlet (described below). If the study process is interrupted, it will be continued at subsequent prenatal visits or by phone when feasible. A flow diagram for the study is shown in Figure 1.

**Figure 1 F1:**
[figure not shown]
IDEAS (Inform, Describe, Educate, Assist, support) for a healthy baby sessions flow diagram PAM, Patient Activation Measure; P-PAM, Parental Patient Activation Measure; NVS: Newest Vital Sign.

### IDEAS intervention

Patients randomized to the patient navigator intervention will participate in the IDEAS for a Healthy Baby’ sessions. The conceptual model for the intervention is shown in Figure 2. The intervention will include:

**Figure 2 F2:**
[figure not shown]
IDEAS for a healthy baby sessions conceptual model.

•Information about the purpose of quality measures.

•Description of how quality of care varies among practices.

•Education about the existence of publicly reported quality data.

•Assistance in navigating and understanding quality-of-care data on the MHQP website.

•Support for informed decision making in health care.

A list of eligible patients is generated each morning. Patients are then approached by one of the patient navigators in the waiting room of the prenatal clinic and offered an opportunity to participate in the study. If interested, informed consent is obtained and baseline data collected. This may take place in the waiting room, an examination room, or an educational office, when available. Patients randomized to the intervention arm then participate in a brief in-person educational session led by the patient navigator, whose experience includes teaching small undergraduate courses. The navigator’s training for the study included developing an understanding of the methods used to develop the quality measures, use of the MHQP website and obtaining informed consent. Both the primary and secondary navigators participated in extensive rehearsal of the intervention with the principal investigator (PI) feedback prior to piloting then enrolling patients. The information sessions include the rationale for quality measurement, how quality varies among practices, and that information about variation is publicly available. The information session is followed by in-person guided use of the MHQP website with the navigator. Each of two guided website sessions last approximately 20 minutes and take place at two prenatal visits. The first session takes place between 20 and 34 weeks gestation and the second 2 to 6 weeks after the first session. The navigator guides the participant in use of the MHQP website on a laptop computer. There is a standard explanation of the meaning of the quality performance measures and patientexperience survey data. The patient navigator provides the same demonstration to all participants about how the website can be used to assess a practice’s performance. Following this standard intervention, patients are shown performance data for practices they would like to view within a 25-mile radius of their home. If the participant does not have any practices she wishes to view, a standard set of three area practices with high and low scores are shown as examples. Practices shown are recorded. A copy of the study information pamphlet is given after the first guided website session and the participant is asked if they have questions about the pamphlet. During the second intervention session, the patient navigator asks if the participant had an opportunity to look at the website themselves. The navigator then invites them to look at local pediatric practice data again and will respond to any questions about performance data for these practices. Participants may complete a worksheet during the intervention in which they fill out a table of scores on performance measures for the practices they review. Patient navigators do not recommend one practice over another but do discuss the practices’ quality scores and what the scores mean. Objectives of the IDEAS for a healthy baby intervention are outlined in Table 2, along with methods to achieve objectives.

**Table 2 T2:** Objectives and associated navigator actions

**Intervention objective**	**Navigator action**
Inform about the purpose of quality measures	Describes concept of quality in language that is meaningful to participants
Describe how quality of care varies	Gives examples of quality measures and range of performance variation; explains potential meaning for child’s health
Educate about the existence of publicly reported health care quality data	Demonstrates several sites with publicly reported quality data, draws analogy to consumer reports
Assist in use of MHQP website	Shows performance measures on website, describes how they are determined, shows local practice data, guides in use
Support for informed decision making	Puts health care quality in the context of other decisions new parents make (such as circumcisionand breast or bottle feeding)

*MHQP* Massachusetts Health Quality Partners.

### Information pamphlet control

The pamphlet will provide information about clinical quality performance measures, patient satisfaction measures, and information about the MHQP website, including the purpose of the site as well as the web address (URL) where the quality-of-care data relevant to pediatric care are located. Participants randomized to the control group will receive the information pamphlet following collection of baseline measures on the day of enrollment.

### Outcome assessment

All enrolled patients will be interviewed after delivery, prior to hospital discharge for outcome assessment. This assessment will include the name of the pediatric practice where the newborn has a scheduled visit (required by Baystate prior to infant discharge) and follow-up measures outlined.

### Measures

#### Primary outcome

The MHQP website uses a star system for rating practices on each of nine measures of pediatric clinical quality with a maximum of four stars. Similarly, the site uses a star system for rating practices on each of seven patient experience measures. A mean quality score and a mean patient experience score will be created for each practice within a 25-mile radius of the hospital that has data reported on the MHQP website for at least three relevant measures. The primary outcomes will be a) the mean MHQP clinical quality and b) mean patient experience scores of the pediatric practices selected by the participants in the navigator intervention compared to the control. All measures are summarized in Table 3.

**Table 3 T3:** Summary of outcome and other measures

	**When completed**	
	**Baseline**	**Post-intervention**
**Primary outcome**		
Clinical quality and patient experience scores of pediatric practice selected for child’s newborn visit		X
**Secondary outcome**		
Importance of factors in selecting a pediatric practice	X	X
PAM/P-PAM	X	X
Challenges encountered using website data		X
**Other factors assessed**		
Demographics (for example, age, race/ethnicity, marital status)	X	
Awareness of health care quality measures	X	X
Use of publicly reported quality data	X	X
NVS - health literacy	X	
NVS - numeracy	X	

*PAM* Patient Activation Measure, *P-PAM* Parental Patient Activation Measure, *NVS* Newest Vital Sign.

#### Secondary outcomes

**Patient activation measures** The Patient Activation Measure (PAM) [30] and Parental Patient Activation Measure (P-PAM) [31] are valid, reliable, uni-dimensional, probabilistic Guttman-like scales that reflect a developmental model of activation. The measures can be used to assess changes in individuals’ levels of activation for self-management of health care [30,31]. Prior studies have shown individual and parental activation can differ for the individual, with parental activation being higher than individual [31]. Interventions with decision aids and to improve access to health care have each improved activation measure scores [32,33].

**Importance of factors in selecting a pediatric practice** As part of the study survey, participants will be asked to rate the importance of several factors in selecting a pediatric practice. Factors will be rated on a five-point Likert scale and will include recommendations of friends or family, advice from a physician, an existing relationship with a provider, insurance, and proximity to home.

#### Other measures

**Demographics** Demographic data collected will include age, race/ethnicity, country of birth, parity, household income, marital status, number of adults in the household, number of children in the household, insurance status, primary language spoken at home, and name of current pediatric practice if the participant has children.

**Use of publicly reported data** As part of the study survey, we will determine participants’ familiarity with health care quality measures, variation in quality of care, awareness of publicly reported health care quality data, and their personal use of publicly reported health care quality data outside of the study.

**Health literacy and numeracy** The Newest Vital Sign (NVS) is a screening tool that assesses general literacy and numeracy skills as applied to health information. Individuals examine information on a nutrition label and answer six questions about how they would interpret and act on that information. The NVS takes approximately 3 minutes to complete.

**Challenges encountered using website data to guide provider choice** At the post-delivery interview, women will be asked what difficulties, if any, they encountered acting upon the information they accessed either with the navigator or on their own using the information pamphlet. Anticipated barriers include limitations imposed by the participant’s insurance carrier and transportation difficulties.

### Analysis

#### Intervention efficacy

Descriptive statistics will be used to characterize the study population and evaluate the distributions of outcomes, predictors and covariates. We will use *t*-tests and Wilcoxon rank-sum tests to compare mean quality and patient experience scores of the pediatric practices selected between women randomized to the navigator intervention and the information pamphlet control. This analysis will be both overall and within strata defined by parity (0, 1+). Our primary analysis will be intent-to-treat, based upon randomization, whether or not the intervention sessions occurred. Patients who choose practices that do not appear on the MHQP website will not be included in the primary outcome analysis but will be included in secondary outcome analyses. Secondary analysis will adjust for compliance with the intervention. We will also evaluate analysis of variance models for the mean quality and patient experience scores, adjusting for parity and any baseline patient characteristics that were not balanced between the intervention groups. An interaction effect for intervention with parity will be included to test for difference in the intervention efficacy between women selecting a pediatrician for the first time versus those with children. Confounding by covariates will be assessed. In addition we will explore the impact of clustering of women within neighborhoods defined by residential zip code, since location of practice relative to home may have a large impact on choice of practice. Final models will provide an estimate of the patient navigator effect on the quality and patient experience ratings of selected pediatric practice, both overall and by parity, adjusting for important maternal characteristics. If practice scores on the website should change during the course of the study, the scores present during the prenatal period will be used in the analysis.

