### Power/sample size

Power was evaluated to detect a difference between intervention groups in mean quality and patient experience ratings of pediatric practices, within strata defined by parity (0, 1+). In an 18-month period, we anticipate 2,250 pregnant women will be seen at the Wesson Women’s OB and Midwifery Clinic. Based upon prior experience with research recruitment in these clinics, we expect to be able to approach about two thirds, or approximately 1,500 women. Of these we anticipate 1,200 will meet age and language eligibility requirements and that 730 will agree to participate, with 650 completing baseline and post-delivery data collection.

Expecting approximately 40% nulliparous women [28], we will need to have at least 130 women in each study arm within strata defined by parity. Quality data were identified on the MHQP website for 18 practices within a 25-mile radius of Springfield, with a mean (SD) quality score of 3.1 (0.5) on nine pediatric measures. Mean (SD) patient experience scores were similar at 3.0 (0.6). Using a significance level of 0.01, we will have power greater than 80% to detect a mean difference of 0.2 units in quality scores between control and intervention, within each stratum of parity. Power is greater than 80% to detect a 0.25 difference in mean patient experience ratings. The magnitude of the differences (0.2, 0.25) would indicate a meaningful difference in mean quality or patient experience rating of practices selected, yet this difference is large enough that we expect it could be detected.

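### The efficacy analysis does not name the score of the current practice of women with children, a baseline value of both primary outcomes, as a covariate; adjusting for it would gain precision at almost no cost

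*Protocol article*

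**What the plan says.** All references are to the protocol article.

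- **Lead comparison (Analysis, Intervention efficacy).** The first-listed efficacy analysis, against the pamphlet control, pairs t-tests with "Wilcoxon rank-sum tests to compare mean quality and patient experience scores of the pediatric practices selected between women randomized to the navigator intervention". It has no covariates. The next sentence begins "This analysis will be both overall and within strata defined by parity (0, 1" and goes on to cover women with one or more children, so the same tests are also run separately in each parity stratum.
- **Models (same section).** Analysis of variance follows, "adjusting for parity and any baseline patient characteristics that were not balanced between the intervention groups". It also has a parity interaction: "An interaction effect for intervention with parity will be included to test for difference in the intervention efficacy". Final models are to give estimates overall and by parity.
- **Baseline data (Other measures, Demographics).** The trial records the "name of current pediatric practice if the participant has children". Under Recruitment and informed consent, baseline data are collected before random assignment.
- **Expected behaviour (Recruitment and informed consent).** Women who already have a practice are expected to be less inclined to switch on quality scores alone, and the text gives this as its reason for stratifying: "Randomization will be stratified based on parity because women who have already selected a pediatric practice for their older children". The Discussion repeats the expectation as the first limitation.
- **Activation outcomes.** Here the plan does adjust for the baseline level of the outcome. It states nothing equivalent for the primary outcomes.

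**The concern.** Each primary outcome is a score attached to a practice. For a woman who already has a practice, the name recorded before randomisation can be looked up on the same website, which gives a pre-treatment value of the same variable. If many such women stay where they are, much of the spread in their outcome was fixed before the navigator met them. That spread is noise for the comparison of arms, and a covariate would remove it.

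The stated rule for admitting covariates would not reliably bring this one in. It selects on observed imbalance, whereas precision depends on how well a covariate predicts the outcome. A strong predictor that happens to be balanced would be left out.

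At stake is precision among women with children. The plan expects less switching there, so a diluted effect is likely. The overall and interaction estimates would also gain.

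**Working it through.** **Inputs from Power/sample size.** 650 completers; about 40% nulliparous; significance level 0.01, sidedness not stated; clinical quality SD 0.5 and difference 0.2; patient experience SD 0.6 and difference 0.25. With equal arms:
- nulliparous: 650 × 0.4 / 2 = 130 per arm
- with children: 650 × 0.6 / 2 = 195 per arm

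**The plan's own figure.** The text says: "Using a significance level of 0.01, we will have power greater than 80% to detect a mean difference of 0.2 units in quality scores" within each parity stratum. By the normal approximation, at 130 per arm:
- two-sided 0.01: 74.2% for clinical quality, 78.3% for patient experience
- one-sided 0.01: 81.6% and 84.9%

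So the claim of more than 80% reproduces at 130 per arm only if the test is one-sided. That is a separate matter. At 195 per arm, two-sided, power is 91.5% and 93.8%.

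**Assumed input.** The correlation r between the baseline practice's score and the chosen practice's score is not in the document. As a guide, suppose a share p of women with children stay (baseline and outcome scores equal) and the rest choose independently from the same distribution. Then the covariance is p × variance, so r = p. A correlation of 0.6 would correspond to 60% staying.

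**Women with children, clinical quality.** Residual SD = 0.5 × √(1 − r²). Detectable difference at 80% power, two-sided 0.01, 195 per arm, noncentral t:

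| r | Variance removed (r²) | Residual SD | Detectable difference | Equivalent sample multiple, 1/(1 − r²) |
|---|---|---|---|---|
| 0 | 0% | 0.500 | 0.174 | 1.00 |
| 0.3 | 9% | 0.477 | 0.166 | 1.10 |
| 0.4 | 16% | 0.458 | 0.159 | 1.19 |
| 0.6 | 36% | 0.400 | 0.139 | 1.56 |
| 0.8 | 64% | 0.300 | 0.104 | 2.78 |

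The normal approximation gives 0.173 unadjusted and 0.165 at r = 0.3.

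**If the true effect among women with children is below 0.2** (same settings):

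| True difference | r = 0 | r = 0.6 | r = 0.8 |
|---|---|---|---|
| 0.12 | 41% | 65% | 91% |
| 0.15 | 65% | 87% | 99% |

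**Overall estimate.** Weight the two stratum estimates 0.4 and 0.6. The variance relative to the unadjusted comparison is then 0.4 + 0.6(1 − r²) = 1 − 0.6r². This gives 0.946, 0.784 and 0.616 at r = 0.3, 0.6 and 0.8.

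**Incomplete coverage.** If only a share c of women with children have a scored current practice, the variance removed in that stratum is roughly c × r². With c = 0.5 and r = 0.6 that is 18%, and the detectable difference is 0.174 × √0.82 = 0.158.

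**Parity alone.** With a mean difference g between strata, parity explains 0.24g²/0.25 of the variance: 1% at g = 0.1 and 9% at g = 0.3. Stratifying the overall test by parity therefore gains little by itself.

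**The case against.** **Parity is already handled.** A reader might infer that the primary comparison ignores the parity strata. The text does not support that. The tests are repeated within strata, the models include parity and its interaction with arm, and power is stated within strata. Only the overall t-test and Wilcoxon test are unstratified, and the arithmetic shows this costs little.

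**Silence on covariates may be condensation.** The plan also says that confounding will be assessed and that final models adjust for important maternal characteristics. Neither phrase rules out the baseline practice score, and a full covariate list usually sits in an analysis plan. This has weight. But the article does state how covariates enter, namely by imbalance, and it does state that the lead tests have none. Those are choices that can be commented on.

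**The size is assumed.** It is tempting to say that most outcome variance among women with children is their existing practice. That needs r above about 0.7, and the plan says only that they may be less likely to change. At r = 0.3 the gain is small.

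**The gain falls where power is not shortest.** At a difference of 0.2 the stratum with children has 91.5% power unadjusted (two-sided), while the nulliparous stratum, which is tighter, gains nothing. This stands at the design difference. It weakens if women who stay dilute the effect, as the power figures at 0.12 and 0.15 show.

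**Adjustment does not separate staying from switching.** Correct: an adjusted mean difference cannot do so, and a switching outcome would be needed. Women who stay also have nearly identical scores before and after, so residuals will not be normal and their variance will differ by parity. The sample multiples are therefore approximate.

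**Conclusion.** The point holds as one of efficiency. The first-listed comparison is unadjusted, its overall version is not stratified by the randomisation factor, later covariates enter by imbalance, and a baseline value of both primary outcomes that can be derived from data already collected is not named in any efficacy analysis. The unadjusted comparison of randomised arms remains valid, and nothing here implies bias.

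For clinical quality among women with children, the detectable difference would fall from 0.174 to between about 0.166 (r = 0.3) and 0.104 (r = 0.8). Across the whole sample, variance would fall by about 5% to 38% over the same range. These figures assume:
- 195 women with children per arm, all choosing a scored practice;
- a baseline score for every one of them;
- an SD among women equal to the 0.5 found across practices;
- a two-sided 0.01 test.

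The 60% share is an upper bound, because a woman may have no current practice or an unscored one. Nulliparous women gain nothing in their own stratum. The change is worth making because it is cheap, but the trial's validity does not depend on it.

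**What to change.** For each primary outcome, prespecify one linear model of the chosen practice's score on:
- arm;
- parity stratum;
- the planned arm-by-parity interaction;
- for women with children, the score of the baseline practice on the same scale, with an indicator where there is no current practice or it is unscored (set to a constant for nulliparous women).

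Report the by-parity estimates, and state how they combine into the overall estimate, for example weighted by stratum share. Use robust standard errors, because residual variance will differ by parity. Apply the same baseline adjustment in the analysis confined to women with children. Keep the t-test and Wilcoxon test as supportive, so that one named analysis decides each outcome. Choose covariates in advance for their expected prognostic value and drop the imbalance rule.

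The cost is revised analysis wording and a lookup of website scores for practices already recorded. No new data collection is needed.
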